##### Physical activity

Physical activity will be assessed with an inertial sensor (DynaPort MoveMonitor Plus, McRoberts BV, The Netherlands) at M0, M4 and M12 [60, 61]. Participants will receive the sensor during the assessment visits at M0, M4 and M12 including corresponding instructions. The sensor will be worn on the lower back for seven consecutive days, preferably day and night, except during water activities, and will afterwards be returned by mail. The sensor includes a tri-axial gyroscope and registers trunk accelerations in vertical, mediolateral and anteroposterior directions, with a sample rate of 100 samples per second and a range of -8 g to + 8 g for a continuous duration of 7 consecutive days. The wearing time of the sensor, the average daily time being upright (i.e. standing and shuffling), in locomotion (i.e. walking, stair walking, cycling) and time spent in sedentary behaviour (i.e. sitting and lying) will be determined. In addition to the amount of daily physical activity, the quality of daily life gait will be calculated from the accelerometry data, as a composite score of characteristics of daily life gait episodes has been shown to be predictive of falls [61]. From the one-week accelerometry data, all locomotion episodes that last 10 s or longer will be selected and divided into epochs of 10 s; gait quality characteristics will be calculated for each of these 10 s epochs. Subsequently, gait quality characteristics will be estimated as median values over the week and the gait quality composite score will be calculated, based on a weighted sum of autocorrelation at stride frequency, power at step frequency, root mean square of the accelerations and index of harmonicity [62].

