### Data management

Every participant will receive a computer-generated unique identification code at baseline. All data will be collected pseudonymised using this identification code. In the data management system, test results from baseline and post intervention assessments will be collected as well as the documentation on each training session, and for each identification code a digital logbook will be kept in the data management system. To improve data quality, a trained project assistant will verify the data entries and check the case report forms in the data management system after all trainings and assessments are finished. If data are missing, the assistant will check the logbook.

Inertial sensor data will be uploaded to the server of the manufacturer of the accelerometers (McRoberts B.V.) for processing of activity classification of physical activity (walking, stairs walking, standing up, shuffling, cycling) and sedentary behaviour (lying, sitting). This classification will be downloaded from the manufacturer’s server and will be saved together with the raw data on a password protected external hard disk.

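### As written, the gait quality score takes in cycling epochs, because it uses all locomotion episodes and the protocol counts cycling as locomotion

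*Protocol article*

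**What the plan says.** The Physical activity section of the protocol article describes two kinds of outcome from the same week of sensor data.

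The first is the amount of activity. One of its categories is time "in locomotion (i.e. walking, stair walking, cycling"). The abbreviation i.e. makes this a definition, not a list of examples.

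The second is gait quality, which the section motivates by saying that "a composite score of characteristics of daily life gait episodes has been shown to be predictive of falls". Its steps are:

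- Selection: "all locomotion episodes that last 10 s or longer will be selected and divided into epochs of 10 s".
- Calculation: "gait quality characteristics will be calculated for each of these 10 s epochs".
- Weekly summary: "gait quality characteristics will be estimated as median values over the week".
- Composite: a "weighted sum of autocorrelation at stride frequency, power at step frequency, root mean square of the accelerations and index of harmonicity".

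The Data management section says that the manufacturer's server returns an "activity classification of physical activity (walking, stairs walking, standing up, shuffling, cycling"), together with sedentary classes. This classification is downloaded and stored with the raw data.

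**The concern.** The selection rule uses a term that the same paragraph has just defined to include cycling. An analyst who follows the text would compute stride and step characteristics on stretches of bicycle riding. Two of the four components are tied to stride or step frequency, and a cyclist produces neither strides nor steps. The other two can be computed on any trunk signal, but on a bicycle they describe cycling.

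What is at stake is the meaning of one secondary outcome. The Discussion says that the secondary outcomes should give insight into the mechanisms behind a reduction in falls. A gait score that also moves with how much a person cycles serves that purpose less well. Two people with identical walking, or one person at two visits, could receive different scores because their cycling differed.

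**Working it through.** **Text check.** The steps, followed in order, are:

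1. Locomotion is walking, stair walking and cycling (Physical activity, amount of activity).
2. All locomotion episodes of 10 s or longer are selected (Physical activity, gait quality).
3. Characteristics are computed on every resulting 10 s epoch and summarised by the weekly median.
4. No sentence in the article restricts step 2 to walking.

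So any cycling episode of 10 s or longer, recorded while the sensor is worn, enters the score. Stair walking enters too, but it is gait, so the mismatch with the construct strictly concerns cycling.

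**Size.** The plan states no figure on this point, so there is none to reproduce. It also gives no walking or cycling times. The minutes below are assumptions, and the calculation is a worst case.

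Let *w* and *c* be minutes per day of walking and cycling in episodes of 10 s or longer. The cycling share of epochs is

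f = c / (w + c).

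Suppose that every cycling epoch lies above all walking values on a characteristic. The pooled median is then the walking value at quantile q, where (1 − f) × q = 0.5, so

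q = 0.5 / (1 − f).

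If every cycling epoch lies below the walking values, the result is the mirror image, 1 − q. Converting q to a normal deviate gives the shift in SDs of one person's walking epochs, assuming normality.

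| w (min/day) | c (min/day) | f | q | Shift (within-person SD) |
|---|---|---|---|---|
| 90 | 5 | 5/95 = 0.05 | 0.528 | 0.07 |
| 30 | 5 | 5/35 = 0.14 | 0.583 | 0.21 |
| 60 | 20 | 20/80 = 0.25 | 0.667 | 0.43 |
| 45 | 30 | 30/75 = 0.40 | 0.833 | 0.97 |
| 60 | 60 | 60/120 = 0.50 | – | median can fall among cycling epochs |
| 30 | 60 | 60/90 = 0.67 | – | median falls among cycling epochs |

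With walking epochs only, f = 0, q = 0.50 and the shift is 0. Participants who do not cycle have f = 0 under either rule.

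**From person to trial.** The effect is the time-by-treatment interaction (Primary and secondary outcomes). Let D be the average change from baseline in an arm's score that is due only to a change in cycling share. The bias in the treatment effect is then D(intervention) − D(control). It is zero when cycling changes alike in both arms, and what remains is extra variation between people and visits.

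**The case against.** **Walking was probably meant.** The bracketed list belongs to the time-in-activity outcome, and the gait step is introduced by reference to gait episodes. Locomotion may simply have been reused loosely. The article also cites sources for the composite and its calculation, and these or the full protocol may restrict the selection. This is a fair reading of intent, and it means that nobody can say from the article that cycling will in fact be processed. It does not repair the text: the article states a selection rule, gives the only definition of its key term, and the two together conflict with the construct. This is a stated rule, not a detail left to another document.

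**The size rests on assumptions.** This stands. The minutes are assumed. Complete separation of cycling from walking values is not shown for any of the four components. The SDs describe one person's epochs on one characteristic; they are neither between-person SDs nor treatment effects. The article does not give the composite's weights, so shifts in different components could add up or partly cancel.

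**Stronger readings that the documents do not support.**

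- A reader might infer that cyclists' scores would come mainly from non-gait data. That needs eligible cycling time to exceed eligible walking time, and the documents say nothing on either, nor on how long cycling bouts last.
- A reader might class stair walking with cycling as non-gait. It is gait, and nothing in the documents supports removing it.
- A reader might expect seasonal change in cycling to produce a false treatment effect. Randomisation is in blocks of 10, so the arms are recruited side by side and season should affect both alike. It adds noise, not systematic bias.
- A reader might infer that the intervention itself changes cycling. The documents do not say so. The Discussion notes that activity can raise exposure to falls, and the control flyer also encourages activity, but neither is described as altering cycling.

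**The consequence is limited.** This also stands. It concerns one secondary outcome, and the Discussion says that the study is not powered for the secondary outcomes. Raw data and class labels are both kept, so the selection can be corrected at analysis.

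**Conclusion.** Wrong as written. The definition of locomotion and the selection rule, read together, put cycling epochs into a score intended to describe daily life gait. That conclusion rests on the text alone and needs no assumption.

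The size is uncertain. For participants who cycle, the weekly median depends partly on their cycling share. The effect is negligible at small shares, about 0.07 within-person walking SD at worst at 5%. It could be large at high shares, such as 0.97 SD at 40% under complete separation and normality. The documents do not show where participants would fall in that range. A between-arm bias requires cycling to change differently by arm; otherwise the cost is noise. The primary falls outcome is unaffected.

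**What to change.** In the gait quality sentence of the Physical activity section, replace the reference to all locomotion episodes with wording such as: *only episodes classified as walking and lasting 10 s or longer are used for gait quality; cycling is excluded*. Add a clause saying whether stair walking is included; either choice can be defended if it is stated. Leave the definition of locomotion as it is for the amount-of-activity outcome, where cycling belongs.

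The change needs no new data collection. Walking, stairs walking and cycling are already separate classes in the downloaded classification, so it amounts to a filter in the analysis code. The only cost is fewer epochs for people who cycle.

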#### Process evaluation

To evaluate the In Balance intervention, participants of the intervention group will be asked to fill in a questionnaire about their expectations of the In Balance intervention at M0 and their experiences with the In Balance intervention directly after ending the intervention and at M12. Also, the experiences of the In Balance therapists will be assessed with a questionnaire after ending the In Balance intervention. To determine adherence, In Balance therapists maintain an attendance list in which the presence of the participants is logged during the In Balance intervention meetings. Participants will also be asked for the frequency and duration they conducted their homework.

### Data management

Every participant will receive a computer-generated unique identification code at baseline. All data will be collected pseudonymised using this identification code. In the data management system, test results from baseline and post intervention assessments will be collected as well as the documentation on each training session, and for each identification code a digital logbook will be kept in the data management system. To improve data quality, a trained project assistant will verify the data entries and check the case report forms in the data management system after all trainings and assessments are finished. If data are missing, the assistant will check the logbook.

Inertial sensor data will be uploaded to the server of the manufacturer of the accelerometers (McRoberts B.V.) for processing of activity classification of physical activity (walking, stairs walking, standing up, shuffling, cycling) and sedentary behaviour (lying, sitting). This classification will be downloaded from the manufacturer’s server and will be saved together with the raw data on a password protected external hard disk.

### Sample size

To obtain a reduction of 50% in the number of falls between the intervention and control group, a minimum of 106 persons are required per group, at a power of 0.80, beta of 0.02 and alpha of 0.05. Taking into account a dropout rate of 20%, the total required sample size is 256 participants. Hence, we expect that about 16 In Balance intervention groups of 8 participants each, are needed to include the required sample size of 128 participants in both the intervention and control group.

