**Methods:**

This study is a single-blinded, multicenter randomized controlled trial. The target sample will consist of 256 community-dwelling non-frail and pre-frail adults of 65 years or older with an increased risk of falls. The intervention group receives the In Balance intervention as it is currently widely implemented in Dutch healthcare, which includes an educational component and physical exercises. The physical exercises are based on Tai Chi principles and focus on balance and strength. The control group receives general written physical activity recommendations. Primary outcomes are the number of falls and fall-related injuries over 12 months follow-up. Secondary outcomes consist of physical performance measures, physical activity, confidence, health status, quality of life, process evaluation and societal costs. Mixed model analyses will be conducted for both primary and secondary outcomes and will be stratified for non-frail and pre-frail adults.

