## Background

Falls are a major cause of mortality and morbidity in older adults [1]. More than one-third of community-dwelling adults aged 65 years or older falls at least once per year [2]. The number of falls is expected to increase even further due to the ageing of the population [3–5]. Falls in older adults often result in injury with 109,000 older adults visiting an Emergency Department due to a fall-related injury in the Netherlands in 2019 [6]. Besides the risk of injuries, falls may also increase fear of falling [7]. Fear of falling may result in a reduction in physical activity in daily life, which can lead to a decreased muscle strength and an increased fall risk [8–11]. Falls and its sequelae can lead to a decreased quality of life up to 9 months after a fall, suggesting that even after that amount of time older adults are still suffering from their fall and its consequences [12, 13]. Fall-related injuries result in considerable healthcare costs, which are estimated at more than 1 billion euros in the Netherlands [6]. On top of these healthcare costs, other costs also have to be taken into account, such as individual expenses, help from family and/or friends and productivity losses due to absence from work or unpaid activities [14–16]. The alarming impact of falls on older individuals, healthcare and our greying society renders the prevention of falls and fall-related injuries highly urgent [17, 18].

Systematic reviews have shown fall prevention programmes to be effective in reducing the risk of falls among older adults [19, 20]. Group interventions appear more effective than individual programmes, because of higher compliance of participants in the group intervention [21, 22]. Despite the evidence that falls can be prevented by fall prevention programmes, barriers for practical implementation may harm the impact of these programmes. It can for example be questioned whether effectiveness maintains after adjustments in the intervention when implemented, which indicates the importance of re-evaluating implemented interventions [18–20].

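### The planned 256 participants do not retain the stated minimum of 106 per group at 20% dropout, and a beta of 0.02 contradicts a power of 0.80

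*Protocol article*

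**What the plan says.** The only justification of the trial's size is in the Sample size section of the protocol article. The target effect is a halving of falls: "To obtain a reduction of 50% in the number of falls between the intervention and control group". For this, "a minimum of 106 persons are required per group, at a power of 0.80, beta of 0.02 and alpha of 0.05". The allowance for loss follows: "Taking into account a dropout rate of 20%, the total required sample size is 256 participants". The section then confirms equal groups, referring to "the required sample size of 128 participants in both the intervention and control group".

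The total of 256 recurs in the abstract ("The target sample will consist of 256 community-dwelling non-frail and pre-frail adults of 65 years or older"), in the number of envelopes under Recruitment, randomization, blinding and treatment allocation, and in the Discussion. None of these places corrects or explains the figures.

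**The concern.** Two statements in one short paragraph conflict with their neighbours.

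- **Dropout.** 106 per group is called a minimum, and 256 is presented as the number that protects it against 20% loss. Losing a fraction d of those randomised leaves n × (1 − d), so the evaluable number has to be divided by (1 − d). The printed total looks as if it was multiplied by (1 + d) instead.
- **Beta.** Beta is one minus power. A power of 0.80 and a beta of 0.02 cannot both be true.

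Readers will judge the primary result, above all a null one, against this paragraph. As printed, they cannot rely on both the 80% power and the 20% dropout allowance, and they meet two incompatible type II error rates. The Discussion itself names dropout as a threat, particularly among controls, so the allowance may well be used.

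**Working it through.** **Inputs, all from the Sample size section:** 106 evaluable per group; dropout 20%; 256 in total, 128 per group; power 0.80; beta 0.02; alpha 0.05. Sidedness is not stated, and two-sided is assumed below.

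**1. Reproducing the printed total**
- n × (1 + d) = 106 × 1.20 = 127.2, rounded up to 128; 2 × 128 = 256. This matches exactly.
- n / (1 − d) = 106 / 0.80 = 132.5, rounded up to 133; 2 × 133 = 266. Rounding only on the total gives 212 / 0.80 = 265. Neither matches.

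**2. What 256 delivers**
- Remaining at 20% dropout: 128 × 0.80 = 102.4, about 102 per group, against a minimum of 106.
- Largest dropout that keeps 106: 1 − 106/128 = 0.172, or 17.2% (22 losses per group).
- Shortfall in randomised participants: 266 − 256 = 10, or 9 if rounded only on the total.

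**3. Effect on power**

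Take 106 per group as giving exactly 80% power, two-sided alpha 0.05, normal approximation. The standardised effect at n = 106 is 1.960 + 0.842 = 2.802, and it scales with the square root of n.
- At n = 102: 2.802 × √(102/106) − 1.960 = 0.788; Φ(0.788) = 0.785.
- Power is therefore about 78.5%, a loss of about 1.5 percentage points.

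**4. Beta**
- Power 0.80 gives beta = 1 − 0.80 = 0.20. Beta 0.02 gives power = 1 − 0.02 = 0.98.
- Power 0.98 would multiply the sample size by ((1.960 + 2.054) / (1.960 + 0.842))² = 2.05, so about 218 evaluable per group.

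**5. Which of the two is the misprint**

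The section gives no control rate, dispersion or test, so this step rests on an assumption. The Background says "More than one-third of community-dwelling adults aged 65 years or older falls at least once per year". Assume one third of controls fall, halved to one sixth, compared as two proportions (pooled variance under the null, no continuity correction):
- Power 0.80: n = [1.960 × √(2 × 0.25 × 0.75) + 0.842 × √(1/3 × 2/3 + 1/6 × 5/6)]² / (1/6)² = 105 per group after rounding up. With 0.33 against 0.165 it is 107.
- Power 0.98: 214 and 217 per group for the same two pairs.

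The printed 106 lies between 105 and 107 and is far from 214. This points to 0.80 as the intended power and 0.02 as a slip for 0.20. Steps 1 to 4 do not depend on this assumption.

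**The case against.** Both inconsistencies stand on the printed figures. What can be argued is their weight.

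- **The loss is small.** It is four persons per group and about 1.5 points of power. This stands: the design, the randomisation and the analysis are unaffected.
- **Dropouts may still contribute data.** Falls are collected by diary and monthly calls, the analysis is by intention to treat, and the mixed models include a time level. A participant who leaves partway may contribute falls up to that point. This stands in part: 80% power is not necessarily lost. But the sample size section makes no such allowance. It treats dropouts as lost and adds participants to replace them, and on that basis it adds too few.
- **The beta figure is a one-digit misprint.** Very probably so. The 218 per group shows what 0.02 would literally mean; nobody planned it. The two figures still cannot stand together.
- **The power of 78.5% rests on assumptions.** It does: 106 giving exactly 80%, a two-sided test and a normal approximation. The shortfall against 106 needs none of these.
- **The multiplication by 1.20 is not stated.** Correct. It is inferred because it reproduces 128 exactly, and the shortfall does not depend on it.

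**Conclusion.** The concern holds on both counts. At the plan's own 20% dropout, 256 randomised leaves about 102 per group against a stated minimum of 106. The total protects that minimum only up to 17.2% dropout, and a full 20% allowance needs 266 (265 if rounded only on the total). The power of 0.80 and the beta of 0.02 contradict each other; 0.20 is almost certainly meant, and this slip does not affect the sample size.

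The practical consequence is modest: about 78.5% power instead of 80% under the assumptions stated in the working, and less of a loss if partial follow-up is used. The correction is still needed, because the paragraph is the trial's only sample size justification and is wrong as printed.

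**What to change.** Keep 256 and correct the wording of the Sample size section:

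- Change beta to 0.20.
- Replace the 20% allowance with what 256 supports, for example: *A total of 256 randomised participants (128 per group) retains 106 per group with up to 17% dropout; at 20% dropout about 102 per group would remain.*
- If a power for the 20% case is added (about 78%), recompute it from the inputs that produced 106 and state those inputs, including sidedness.

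This costs only a text change and a slightly less favourable dropout allowance. The abstract, the envelope count and the Discussion can stay as they are.

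If the sponsor prefers to keep the 20% allowance, the alternative is to randomise 266. That means ten more participants, changes wherever 256 appears, more envelopes, and 17 intervention groups of eight instead of 16 (133 / 8 = 16.6).

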### Statistical analysis

Data will be analysed using SPSS (SPSS Inc., Chicago, IL, USA), RStudio (Version 1.3.1073) and MATLAB (version R2021a; MathWorks Inc., Natick, MA, USA). All analyses will be performed according to the intention-to-treat principle. Numbers and reasons for drop-out and for missing data on the primary outcome will be provided.

